# Clip placement to prevent delayed bleeding after colonic endoscopic mucosal resection (CLIPPER): study protocol for a randomized controlled trial

**DOI:** 10.1186/s13063-020-04996-7

**Published:** 2021-01-18

**Keywords:** Prophylactic clipping, EMR, Colonic polyp, Delayed bleeding, Clip artifact

## Abstract

**Background:**

Endoscopic mucosal resection (EMR) for large colorectal polyps is in most cases the preferred treatment to prevent progression to colorectal carcinoma. The most common complication after EMR is delayed bleeding, occurring in 7% overall and in approximately 10% of polyps ≥ 2 cm in the proximal colon. Previous research has suggested that prophylactic clipping of the mucosal defect after EMR may reduce the incidence of delayed bleeding in polyps with a high bleeding risk.

**Methods:**

The CLIPPER trial is a multicenter, parallel-group, single blinded, randomized controlled superiority study. A total of 356 patients undergoing EMR for large (≥ 2 cm) non-pedunculated polyps in the proximal colon will be included and randomized to the clip group or the control group. Prophylactic clipping will be performed in the intervention group to close the resection defect after the EMR with a distance of < 1 cm between the clips. Primary outcome is delayed bleeding within 30 days after EMR. Secondary outcomes are recurrent or residual polyps and clip artifacts during surveillance colonoscopy after 6 months, as well as cost-effectiveness of prophylactic clipping and severity of delayed bleeding.

**Discussion:**

The CLIPPER trial is a pragmatic study performed in the Netherlands and is powered to determine the real-time efficacy and cost-effectiveness of prophylactic clipping after EMR of proximal colon polyps ≥ 2 cm in the Netherlands. This study will also generate new data on the achievability of complete closure and the effects of clip placement on scar surveillance after EMR, in order to further promote the debate on the role of prophylactic clipping in everyday clinical practice.

**Trial registration:**

ClinicalTrials.gov NCT03309683. Registered on 13 October 2017. Start recruitment: 05 March 2018. Planned completion of recruitment: 31 August 2021.

**Supplementary Information:**

The online version contains supplementary material available at 10.1186/s13063-020-04996-7.

## Background

### Delayed bleeding after endoscopic mucosal resection

In 2014, a national colorectal cancer screening (NCCS) program was introduced in the Netherlands [1]. The program is based on immunological fecal occult blood testing (iFOBT), followed by colonoscopy after a positive iFOBT result. During colonoscopy, the detection of colorectal cancer and advanced adenomas has been found to be 8% and 43%, respectively [2]. The treatment of advanced adenomas has resulted in a considerable spin-off of the NCCS program.

Endoscopic mucosal resection (EMR) is a safe and cost-effective method for resecting larger flat or sessile adenomas in the colorectum with no signs of submucosal invasion. However, delayed bleeding (DB) is the most prevalent complication and is reported in up to 12% after EMR. Identified risk factors of DB after EMR are anticoagulant drug use within 7 days of the procedure (OR 6.3; *P* = 0.005), polyp size and location in the colon with a 12% incidence rate of delayed bleeding in the cecum, 10% in the proximal ascending colon, 7% at the hepatic flexure, and 2–3% in the left colon [3–9].

Several preventive measures have been undertaken to reduce post-EMR bleeding, such as coagulation of visible vessels, prophylactic clipping (PC), or suturing of the EMR resection defect. Prophylactic coagulation of visible vessels in the resection defect has not been shown to decrease the incidence of DB [7]. However, PC has been reported in several studies to reduce DB especially in right sided EMR’s for lesions sized over 2 cm [10, 11]. Theoretically, a clip applies pressure to the underlying vessels in the EMR defect and results in increased mucosal healing [12], which may result in a reduced DB risk. Nonetheless, studies reporting on PC in EMR have several limitations, such as a retrospective design, inclusion of all sizes and types of polyps (pedunculated/flat, right/left-sided), lack of statistical power, and all reported studies were performed in tertiary referral centers, thereby not representing normal daily practice. Additionally, PC will lead to increased costs of EMR and it is unknown whether the additional costs of PC in high-risk patients (right sided flat polyps ≥ 2 cm) will outweigh the benefits of PC in terms of quality of life gains and/or cost savings related to prevention of DB [12].

### Scar surveillance

After piecemeal EMR, guidelines recommend surveillance colonoscopy after 6 months to evaluate the presence of residual adenoma [13]. Nonetheless, examining post-EMR scars with white-light endoscopy alone may miss up to 30% of recurrences revealed by random biopsy [14, 15]. Thorough inspection of the scar area with enhanced imaging (e.g. NBI, I-scan, etc.) is one of the techniques to determine the presence of recurrence.

With PC, the apposition of the defect margins with clips may cause a different appearance of the scar leading to difficulty in assessing a potential recurrence. This clip-induced scar pattern occurs in 30% of the EMR sites and is described as a “clip artifact”: a bumpy scar that has a normal pit pattern and is normal on biopsy [14, 15]. The occurrence of clip artifacts may therefore increase the difficulty of detecting recurrences.

### Aims

We designed a nationwide randomized controlled trial aiming to compare PC after EMR to standard EMR care without PC for the prevention of clinically significant DB < 30 days. In addition, we aimed to determine DB severity, rates of recurrent and residual adenoma and clip artifacts after PC, and cost-effectiveness compared with standard care.

## Methods

### Trial design

The CLIPPER trial is a nationwide multicenter randomized, parallel-group, patient-blinded superiority trial, comparing prophylactic clipping after EMR to standard care in 356 patients undergoing EMR for a non-pedunculated polyp in the proximal colon sized 20–60 mm in 19 hospitals of the Dutch EMR Study Group in the Netherlands. The trial will be conducted over a time period of 3 years. The study protocol was written in accordance with the SPIRIT guidelines [16, 17].

### Eligibility criteria

Patients aged ≥ 18 years undergoing EMR of a flat or sessile colonic polyp (Paris classification 0-IIa/b/c, Is) measuring 20–60 mm and located proximal from the splenic flexure who gave written informed consent prior to EMR are eligible for inclusion in the study.

A subject with any of the following exclusion criteria prior to randomization will be excluded from participation in this study:
PregnancyActive inflammatory colonic conditions (e.g., inflammatory bowel disease)American Society of Anesthesiology (ASA) grades IV–VPrevious resection or attempted resection of a lesion less than 30 days agoEMR for residual adenoma still in place after a previous intervention> 1 lesion to be removed in the same sessionInvolvement of the cecal valve or orificium of the appendixEndoscopic appearance of invasive malignancy (non-lifting Kato D, Kudo V pit pattern)Macroscopic non-radical resectionClip deployed prior to the completion of the EMR for a perforation or a major intra-procedural bleeding that cannot be treated with coagulation

### Trial treatment

#### Standard care: no PC

Applying snare tip soft coagulation to the margins of the post-EMR defect is often used as preventive treatment for recurrence and may be applied at the endoscopists’ discretion. Anticoagulant use will be managed according to the Dutch Society of Gastroenterologists guideline 2016 [18].

#### Intervention: PC

PC is standardized using Quick Clip Pro - Single Use Repositionable Clips (Olympus, Japan) and is performed in a zipper fashion (Fig. 1). Successful PC is defined as complete closure of the resection defect with aligning clips placed 0.5–1.0 cm apart (Figs. 1 and 2) [10, 19]. After PC, a picture of the final result is made.

**Fig. 1 Fig1:**
[figure not shown]
Prophylactic clip closure in a zipper fashion. **a** A mucosal defect after EMR. In **b**, two clips are placed in a zipper fashion, approximating the defect margins. In **c**, clipping is complete after six clips have been placed in a zipper fashion

**Fig. 2 Fig2:**
[figure not shown]
EMR defects with prophylactic clip closure. **a** A mucosal defect after EMR. In **b**, the EMR defect from A has been approximated with three clips. **c** Another mucosal defect after EMR. In **d**, the EMR defect from **c** has been closed with four clips

All patients will receive normal standard of care in terms of day of discharge, instructions at discharge, outpatient clinic visits to discuss pathology reports, and additional treatment.

#### Surveillance

Six months after EMR, a surveillance colonoscopy is performed, during which the endoscopic characteristics of the scar are determined by the endoscopist and biopsies of the scar are collected to determine residual or recurrent adenoma. In case of an aberrant scar morphology, multiple biopsies of the lesion are taken with a standard biopsy forceps. Lesions suspect for adenoma will be treated directly following the local protocol. The resected fragments will undergo histological analysis. Any other irregularities in and around the scar will be biopsied separately.

### Study end points

The primary outcome is the incidence of clinically significant DB, defined as anal blood loss occurring after the completion of the procedure necessitating emergency department consultation, blood transfusion, prolongation of hospital stay, re-hospitalization, or re-intervention (either repeat endoscopy, angiography or surgery) [5, 10, 20–23]. Self-limiting bleeding managed on an outpatient basis is not considered to be DB.

PC may improve patients’ health status, prevent serious complications of DB, reduce the demand for healthcare, and lower costs. The secondary outcomes therefore are (1) severity of DB (see Supplementary File 1 for definition of DB severity), (2) procedure time, (3) perforation rate, (4) EMR scar evaluation at the first surveillance colonoscopy after 6 months, (5) adenoma recurrence rate at 6 months, (6) health-related quality of life, and (7) direct and indirect costs related to PC.

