### Sample size considerations

DB incidence after EMR in the right colon has been reported to range between 7 and 12.7% after EMR [6, 7]. Based on these studies, we believe that PC after standard EMR may be able to reduce delayed bleedings by 7.8% (from 9.8 to 2%) in a superiority design. With a 2-sided significance level of 5% (0.1% used as symmetric stopping boundaries during the interim-analysis, and 4.9% used as nominal significance level) and power of 80%, a total of 310 patients are required. With an estimated drop out of 15%, a total of 356 patients (2 × 178) are required to demonstrate this effect.

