### Assignment of interventions

#### Randomization and treatment allocation

Randomization will take place in a 1:1 ratio after complete radical EMR without a clinically indicated intraprocedural clip placement, using a web-based randomization module (Castor EDC, Amsterdam, The Netherlands). Participants are stratified by center with random block sizes of 2, 4, and 6 per stratum. A time schedule for the trial can be found in Table 1.

**Table 1 Tab1:** Schedule of enrolment, interventions, and assessments

	Study period						
	Enrolment	Allocation	Post-allocation				Close-out
Timepoint	Week − 1	EMR + 0	EMR+ 0	+ 1 month	+ 3 months	+ 6 months	+ 6 months

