### Statistical analysis methods

#### Primary analysis

Comparison of the primary endpoint DB will be performed according to intention-to-treat, using a mixed model regression analysis to correct for clustering of data, resulting in an estimated relative risk and 95% confidence intervals. Scale variables will be presented as mean ± standard deviation and in case of skewed distributions as median and range. Values will be compared by Student’s *T* test, Wilcoxon rank sum test, *χ*^2^ test, or Fisher exact test as appropriate. A two-tailed *p* value < 0.05 is considered statistically significant. A type 1 error will be controlled for by only taking one presentation of the primary endpoint (DB) per patient in the statistical analysis. In case of multiple presentations for bleeding, the highest gradation for severity will be included in the analysis. The outcomes of the intention-to-treat analysis will be compared to an exploratory per-protocol analysis.

In case of disbalances in baseline characteristics, potential confounders for DB will be determined with a *χ*^2^ test or unpaired *t* test where appropriate. Correction for potential confounders with a *p* ≤ 0.15 will be performed using multiple regression analysis. Considering the expected incidence of DB, the statistical power will allow to correct for two confounding factors. We expect at least anticoagulant medication to be a potential confounder for DB.

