#### Analyses of secondary outcomes

The secondary endpoints will be compared between study groups using Student’ *T* test or *χ*^2^ test whenever appropriate. Lastly, a cost-effectiveness analysis will be performed. As a societal perspective allows for a more complete economic evaluation as compared to a health care perspective alone, three cost categories will be analyzed: direct medical costs, direct non-medical costs, and indirect costs (see Supplementary File 1 for a definition of these secondary endpoints).

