## Discussion

The CLIPPER trial has been designed to determine whether PC is effective in preventing clinically significant DB after EMR of large proximal colorectal polyps. The current study design was improved by considering and discussing potential drawbacks of published or ongoing trials with the principal investigators. The following suggestions were made and implemented in the CLIPPER study design:
Randomization after EMR. In this way, non-radical EMRs are not included in the intervention arm and therapeutic clipping for perforation or intraprocedural bleeding can be performed to the discretion of the endoscopist without causing cross-over. The reasons for exclusion of a non-randomized patient after informed consent are registered [32].Inclusion of patients with only one polyp, instead of multiple, enables one to estimate the pure effect of PC on DB and its severity [32].Inclusion of only right sided polyps, which are shown to be associated with a higher DB rate and significant decrease of DB after PC [32, 33].Inclusion of polyps sized 20–60 mm. Previous studies have shown no effect of PC for smaller polyps [34–36], and polyps over 60 mm were excluded in view of feasibility of complete closure [33].Cost-effectiveness analysis. Some studies have predicted cost-effectiveness of PC based on economic models [37, 38]. We will analyze cost-effectiveness based on healthcare utility questionnaires and clinical data.Follow-up period of 6 months. Previous studies have reported that clips can affect scar formation and cause clip artifacts that can be hard to distinguish from recurrent polyp tissue [14]. In order to determine these late clip effects, we included the first surveillance colonoscopy 6 months post-EMR in the follow-up period.

A potential drawback of this study is caused by the timing of the informed consent. In Dutch daily clinical practice, most polyps in the lower range of these inclusion criteria, especially the 2–3 cm polyps, will already be removed by EMR in the same session. As it would neither be ethical nor feasible to approach all colonoscopy patients for informed consent, we will likely include more 3–6 cm lesions undergoing repeat colonoscopy for EMR than 2–3 cm lesions. This needs to be taken into account when interpreting our results.

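### Procedure time is tested unadjusted although allocation follows the EMR; if the whole procedure is timed, the comparison is unbiased but less precise than it need be

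*Protocol article*

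**What the plan says.** Under Study end points, the article lists seven secondary outcomes. The second is given only as "2) procedure time", with no start or stop point.

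Under Randomization and treatment allocation: "Randomization will take place in a 1:1 ratio after complete radical EMR without a clinically indicated intraprocedural clip placement". The Discussion presents "Randomization after EMR" as a deliberate design choice.

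Under Analyses of secondary outcomes: "The secondary endpoints will be compared between study groups", by t test or chi-square test as appropriate. No covariate is named. The adjustment for baseline imbalance described under Primary analysis concerns confounders for delayed bleeding. That section also states: "Scale variables will be presented as mean ± standard deviation and in case of skewed distributions as median and range". It allows a rank test, which is equally unadjusted.

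The secondary-outcomes section ends with a pointer: "see Supplementary File 1 for a definition of these secondary endpoints". It follows the three cost categories, so it is unclear whether it reaches procedure time. Under Study end points, the same file is cited for the severity of delayed bleeding only.

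**The concern.** Because allocation comes after the resection, insertion, inspection and removal of the lesion are finished before the arms can differ. Only the interval from randomisation to the end of the procedure can carry an effect of clipping.

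The article's own usage suggests that the procedure includes the resection: a clip placed during the EMR, before randomisation, is called intraprocedural. Read that way, procedure time is the sum of a part that clipping cannot change and a part that it can. Eligible lesions run from 20 to 60 mm, a threefold range in diameter, and randomisation is stratified by centre but not by lesion size. The first part may therefore vary considerably between patients, and a plain two-group test removes none of that variation.

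At stake is how sharply the trial can state the endoscopy time that clipping adds, a practical burden of the intervention in a trial meant to inform everyday practice.

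**Working it through.** The article gives no mean, SD, target difference or power for procedure time, so there is no stated figure to reproduce. What follows shows how the answer moves with inputs that have to be assumed.

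**Inputs from the article**
- Sample size: "a total of 356 patients (2 × 178) are required to demonstrate this effect", so n = 178 per arm; before the dropout allowance, 310 in total, or 155 per arm.
- Two-sided significance level 0.05 (Primary analysis).

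**Assumed inputs, not in the article**
- SD of pre-randomisation time: 15, 20, 30 or 40 min.
- SD of post-randomisation time: 5 min in both arms, independent of the first phase.
- Added clipping time: 5, 8 or 10 min.

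**Formulas**
- SD of total time = √(SD_pre² + SD_post²)
- SE of the difference = SD × √(2/n); with n = 178, √(2/178) = 0.106
- 95% CI half-width = 1.96 × SE
- Power = Φ(added time / SE − 1.96)

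**Worked case, SD_pre = 20 min.** Total SD = √(400 + 25) = 20.6 min. SE = 20.6 × 0.106 = 2.19 min. Half-width = 1.96 × 2.19 = 4.3 min. Power for 5 min = Φ(5/2.19 − 1.96) = Φ(0.33) = 0.63.

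**Results with 178 per arm**

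| Time analysed | SD (min) | CI half-width (min) | Power, 5 min | Power, 8 min | Power, 10 min |
|---|---|---|---|---|---|
| Total, SD_pre 15 | 15.8 | 3.3 | 0.85 | 1.00 | 1.00 |
| Total, SD_pre 20 | 20.6 | 4.3 | 0.63 | 0.96 | 1.00 |
| Total, SD_pre 30 | 30.4 | 6.3 | 0.34 | 0.70 | 0.87 |
| Total, SD_pre 40 | 40.3 | 8.4 | 0.22 | 0.47 | 0.65 |
| Post-randomisation only | 5.0 | 1.0 | about 1.00 | about 1.00 | about 1.00 |

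With 155 per arm, power for 5 min on total time is 0.80, 0.57, 0.30 and 0.19 across the four values of SD_pre.

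**Share of variance fixed before allocation.** SD_pre² / (SD_pre² + SD_post²) is 225/250 = 90% at SD_pre 15 and 1600/1625 = 98% at SD_pre 40.

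**Bias.** Randomisation balances pre-randomisation time in expectation. The expected difference in total time therefore equals the expected difference in post-randomisation time, and only the precision differs.

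**Effect of adjustment.** Total time is pre-randomisation time plus post-randomisation time. A linear regression of total time on arm and pre-randomisation time therefore gives exactly the same arm coefficient as a regression of post-randomisation time on the same two variables. Adjusting for pre-randomisation duration thus recovers essentially all of the lost precision. Adjusting for lesion size recovers only the part of the variance that size explains.

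**The case against.** The strongest objection is that the article never says the whole procedure is timed. It names the endpoint in two words, and start and stop points are the kind of detail that an article leaves to the full protocol, the case record form or an analysis plan. This stands. The absence of a definition is therefore not the point, and the finding is conditional on the natural reading.

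Second, a reader might infer that most of the measured time precedes allocation and that the comparison therefore hides or distorts the time cost of clipping. The documents do not support this. They give no durations, and the comparison is unbiased. A chance imbalance in lesion difficulty is ordinary sampling error, which the confidence interval already reflects.

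Third, every SD and every added time above is assumed. This also stands. At a pre-randomisation SD of 15 to 20 min, an added time of 8 to 10 min would be detected with power of at least 0.96 even on total time.

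Fourth, total time is a legitimate measure of room use in a pragmatic trial, and the Economic evaluation section bases the price of clipping on the clip price without mentioning procedure time. So total time deserves to be reported, and no consequence for the cost analysis can be shown.

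None of this removes the remaining point. The only analysis stated for this outcome is unadjusted, and this trial's randomisation point makes a sharper one available at little cost.

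**Conclusion.** The point holds as a minor matter of precision on one of seven secondary outcomes. If procedure time covers the whole procedure, the planned unadjusted test is valid but wastes precision, and a modest added time can be missed. Under the stated assumptions, the confidence interval for total time is about 3 to 8 times as wide as that for post-randomisation time (3.3/1.04 to 8.4/1.04), and power for 5 added minutes falls below 80% at three of the four SDs tried.

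These figures rest on assumed SDs, on independence of the two phases and on normal approximations. If the supplement or full protocol already starts the clock at randomisation, the point falls away. It has no bearing on the primary endpoint or its analysis.

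**What to change.** State the start and stop points of procedure time, and make two changes to its analysis:

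1. Where time stamps exist, compare the time from randomisation to the end of the procedure between arms. The web-based randomisation module should be able to supply the start time.
2. For all patients, analyse total procedure time by a regression on arm, adjusted for pre-randomisation duration or, if that was not recorded, for lesion size, which eligibility already requires to be assessed. Report total time descriptively as well.

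The cost is a change of endpoint wording and at most one time field on the case record form; the conduct of the trial does not change. There are two downsides. Time from randomisation includes a short log-in delay, present in both arms. Time stamps may also be missing for some of the 217 of 356 patients (61%) already randomised when the article was written; the size-adjusted analysis of total time is the fallback for them, with a smaller gain in precision.
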